## Abstract

**Background:**

Dynamic risk estimations may enable targeting primary prevention of overweight and overweight-related adverse cardiometabolic outcome in later life, potentially serving as a valuable addition to universal primary prevention. This approach seems particularly promising in young children, as body mass index (BMI) changes at a young age are highly predictive of these outcomes, and parental lifestyle interventions at a young age are associated with improved long-term outcome.

**Objective:**

This paper describes the design of our study, which aims to develop digitized tools that can be implemented in the Dutch Child Health Care (CHC) system or by pediatricians for children up to 6 years of age. These tools will enable (1) dynamically predicting the development of overweight, hypertension or prehypertension, low high-density lipoprotein cholesterol (HDL-C) values, and high total cholesterol to HDL-C ratio by early adolescence and (2) identifying children who are likely to have poor cardiometabolic outcome by the age of 5-6 years and by the age of 10 years.

**Methods:**

Data will be obtained from the Generation R (n=7893) and Prevention and Incidence of Asthma and Mite Allergy (PIAMA; n=3963) cohorts, two Dutch prenatally recruited cohorts. We will select candidate predictors that can be assessed during the first visit and/or during subsequent visits to the CHC center or pediatrician, including sex; parental age, education level, and BMI; smoking exposure; ethnicity; birth weight; gestational age; breastfeeding versus formula feeding; and growth data through the age of 6 years. We will design dynamic prediction models that can be updated with new information obtained during subsequent CHC visits, allowing each measurement to be added to the model. Performance of the model will be assessed in terms of discrimination and calibration. Finally, the model will be validated both internally and externally using the combined cohort data and then converted into a computer-assisted tool called *Pro***C**OR (Prediction Of Child CardiOmetabolic Risk).

**Results:**

This is an ongoing research project financed by the Dutch government. The first results are expected in 2016.

**Conclusions:**

This study may contribute to the national implementation of digitized tools for assessing the risk of overweight and related cardiometabolic outcome in young children, enabling targeted primary prevention, ultimately yielding relevant health gains and improved resource allocation.

## Introduction

The prevalence of childhood overweight and obesity is increasing worldwide, including the Netherlands [1,2]. Hypertension or prehypertension and low high-density lipoprotein cholesterol (HDL-C) values are related adverse cardiometabolic risk factors that are also highly prevalent in children. The prevalence of hypertension is approximately 3.5%, 9%, and 19% among normal weight, overweight, and obese children, respectively [3-5]. Moreover, 6.2% of normal weight children have low HDL-C levels [6]. Overweight, hypertension, and low HDL-C level in childhood generally persist into adulthood, but are usually asymptomatic. Importantly, the presence of these risk factors in childhood can be detrimental, increasing the lifetime risk of developing severe health complications such as coronary heart disease and type 2 diabetes [7-14].

Once an individual becomes overweight, this condition is usually difficult to reverse, even among children, as changing one’s lifestyle is difficult, and people often revert to their old habits resulting in even poorer health due to weight fluctuations [15]. Therefore, the European Society of Cardiology states that *primary* lifelong prevention of overweight and related poor cardiometabolic outcome deserves high priority beginning at birth [16]. Primary preventive interventions are particularly important in children aged less than 6 years, as changes in body mass index (BMI) below this age are more predictive of later overweight and poor cardiometabolic outcome than BMI changes after this age [17,18]. Moreover, parental lifestyle interventions when the child is young are associated with improved long-term outcome [19]. In addition, the American Academy of Pediatrics found that early intervention can yield better success in children with high cardiometabolic risk [20,21].

The EPODE (Ensemble Prévenons l’Obésité Des Enfants) program in northern France is a universal primary approach designed to prevent overweight in children by involving the family unit and society as a whole, for example, by changing the environment and influencing social norms. The merits of this approach have clearly been demonstrated [22]. Therefore, the program was successfully adopted, converted, and implemented in the Netherlands as the Youth on Healthy Weight (in Dutch: *Jongeren op Gezond Gewicht*, or JOGG) program [23]. Despite the introduction of this program, however, the prevalence of overweight remains relatively high, particularly among children from a low socioeconomic background [24]. Therefore, in addition to this universal approach, there is increasing interest in targeting primary prevention to children with the highest risk of becoming overweight and developing related poor cardiometabolic outcome. These risks may be estimated using prediction models or so-called “clinical prediction rules,” which use the best possible combination of risk factors to calculate the likelihood of a specific outcome.

Prototypes of such prediction models have been developed in the Netherlands within two Dutch cohort studies - the Prevention and Incidence of Asthma and Mite Allergy (PIAMA) birth cohort study and the Terneuzen cohort study - and in other countries, including India [25]. The two aforementioned Dutch prototypes are based on the presence of several predictors at birth, including paternal and maternal BMI [26], and on the trajectory of BMI standard deviation scores (BMI SDS) from 2 to 6 years of age [27]. Both Dutch prediction models have fair performance, indicating that targeted primary prevention of overweight and related poor cardiometabolic outcome is feasible with the help of evidence-based prediction models [26,27].

Here, we present the design of our study, which aims to develop dynamic prediction models to estimate the risk of young children (up to 6 years of age) developing overweight, hypertension or prehypertension, low HDL-C levels, and/or a high total cholesterol to HDL-C ratio by early adolescence. The resulting prediction models will be converted into easy-to-use tools called *Pro*
**C**OR (PRediction Of Child CardiOmetabolic Risk), which can be applied both in the Dutch preventive Child Health Care (CHC) system and by pediatricians.

Because the Dutch CHC reaches more than 95% of all children of all ethnicities through 16 regular visits from birth until the age of 6 years, this approach will enable targeted primary prevention for children in this age group. The *Pro*
**C**OR tools will provide risk estimations by taking into account the accumulation and changes in exposure to multiple risk factors throughout life, including familial risk factors [28], smoking exposure, physical inactivity, and changes in BMI [29].

Because we cannot exclude the possibility that children may already have an adverse cardiometabolic profile at this young age, thereby indicating the need for treatment, our secondary aim is to develop risk estimation models to assess the need for further diagnostics of poor cardiometabolic outcome at age 5-6 years and at age 10 years, two ages at which regular visits are made to the Dutch CHC centers.

The study design includes (1) data collection; (2) the development, external validation, and, if required, updating of dynamic prediction rules within two large Dutch cohort studies; and (3) an assessment of whether the resulting tools can be implemented in practice. Therefore, the study will also focus on risk communication, as this is an important aspect that can affect the likelihood of successful implementation.

The outcomes of the prediction rules will be assessed in early adolescence, because BMI SDS values measured between 10 and 18 years of age are highly correlated with adult BMI SDS values and body fat mass [17]. Moreover, as discussed above, hypertension/prehypertension, low HDL-C levels, and high total cholesterol levels often persist from childhood into adulthood, particularly from adolescence [10-12]. Our study proposal has been awarded a TOP Prevention Grant from ZonMw (title: “Targeted primary prevention of overweight and cardiometabolic risk using dynamic risk assessments from infancy onward in Child Health Care”; 200500006) , offering the opportunity to innovate in terms of both content and collaboration. See Multimedia Appendices 1, 2 and 3 for the reviewers’ comments on the original version of the research proposal.

## Methods

### Stakeholder Group

For the study results to be useful, the developed tools must ultimately be implemented in practice. Therefore, a group of stakeholders has been established and comprises CHC physicians and nurses, pediatricians, general practitioners, dieticians, epidemiologists, programmers, scientists, and policy makers. In several phases of the study, parents will also be involved to ensure maximum communication regarding risk assessments with parents and maximum implementation of the *Pro*
**C**OR tools in the CHC.

### Design and Setting

This study is embedded in the Generation R (n=7893) and PIAMA (n=3963) cohorts. These large, longitudinal Dutch cohorts provide independent datasets with many uniform variables regarding fetal life, pregnancy, birth, and early growth.

The Generation R study is a population-based, multiethnic cohort study composed of children born to 9778 mothers living from 2002 through 2006 in Rotterdam, the Netherlands [30]. Of all children who were eligible at the time of birth (n=7893), 61% participated in the follow-up study. In this cohort, children of diverse ethnic origins are well represented, including Caucasian (56%), Surinamese (9%), Turkish (7%), and Moroccan (6%) children. Three questionnaires were sent to the participating mothers during their pregnancy. Questionnaires were also sent when the child was 2, 6, 12, and 18 months of age and 2, 3, 4, 5, and 7 years of age. During pregnancy, the participants visited the research center in early, mid, and late pregnancy. From birth through 5 years of age, data regarding growth, development, and medical conditions among the Generation R participants were collected during their routine visits to the CHC centers. At the age of 5-6 years, all participating children and their parents were invited to visit the research center for a medical examination. The data collection of children 9-10 years of age was recently completed.

The PIAMA birth cohort is a population-based prospective cohort comprising 4146 women who were pregnant at baseline [31]. Because 183 women were lost to follow-up before any data regarding the child were collected, the study began with 3963 newborn children who were born in 1996-1997 in various regions of the Netherlands. Questionnaires were sent to the participants during pregnancy, when the child was 3 months of age, annually thereafter from 1 through 8 years of age, and at 11, 14, and 17 years of age. At 8, 12, and 16 years of age, subgroups of participating children were invited for a medical examination. The cohort consists primarily of Caucasians and includes children from both urban and rural areas [31].

Both the Generation R study and the PIAMA study were conducted in accordance with the guidelines established by the Declaration of Helsinki and were approved by the respective medical ethics committees (MECs). Written informed consent was obtained from all participating parents. The MEC for the Generation R study was the MEC of Erasmus Medical Center (MEC 217.595/2002/202). The MECs of the participating institutes for the PIAMA cohort were MEC Rotterdam (132.636/1994/39, 137.326/1994/130 and P04.0071C/MEC 2004-152), MEC Groningen (94/08/92, P04.0071C/ M 4.019912, June 28, 2004, and 12-019/K), and MEC-TNO Utrecht (95/50, February 28, 1996, CCMO Utrecht P000777C, 2000, P04.0071C, 2004, 07-337/K, May 20, 2008, and 12-019/K, May 25, 2012).

### Overweight and Poor Cardiometabolic Outcome

The outcomes of the dynamic prediction models measured at age 10-15 years are as follows:

overweight, defined using the International Obesity TaskForce (IOTF) cutoff values [32];abdominal overweight, defined based on the findings of the Fifth National Growth Study in the Netherlands, which will be available in the near future [2];hypertension or prehypertension, based on systolic and diastolic blood pressure and defined by the National High Blood Pressure Education Program Working Group on High Blood Pressure in Children and Adolescents [33]; andlow HDL-C level or high total cholesterol to HDL-C ratio, in which low HDL-C is defined as <0.9 mmol/L and high total cholesterol is defined as >6.3 mmol/L. Because total cholesterol to HDL-C ratio in childhood quite accurately predicts subclinical adult atherosclerosis, including coronary heart disease, it will be useful to obtain both total cholesterol and HDL-C values [13,14].

The outcomes of the risk estimation models at ages 5-6 years and 10 years are hypertension or prehypertension and a low HDL-C level and high total cholesterol to HDL-C ratio, according to the aforementioned definitions.

### Candidate Predictors

The candidate predictors that were used to develop the two Dutch prototypes [26,27] will also be used to develop the new prediction models. In addition, other candidate predictors will be selected from the literature, including relatively novel risk factors such as child’s height and gross motor skills [34,35]. The stakeholder group will also provide advice—via discussion rounds—regarding the final selection of clinically relevant candidate predictors. The candidate predictors can be divided into the following two categories: (1) predictors that are currently routinely collected by the CHC and (2) predictors that may be routinely collected by the CHC in the near future.

The candidate predictors for the dynamic prediction models are as follows:

Demographics and general characteristics

Sex and ethnicity of the child, urbanization grade, parity of the mother, and the education level and age of both parents.

Prenatal/perinatal factors

Child characteristics: birth weight, gestational age, head circumference, Apgar scores (at 1 and 5 minutes), meconium in the amniotic fluid, formula feeding immediately after birth.Parent characteristics: cesarean or vaginal delivery, use of vitamins and/or minerals by the mother, smoking (including second-hand smoke exposure), BMI of the mother before and after pregnancy, BMI of the father, and blood pressure of both parents.

At the age of 3 months

Body weight and body length, smoking exposure, and breast milk and/or formula.

At the age of 1 year

Body weight and height, smoking exposure, breast milk and/or formula, data from the food frequency questionnaire (FFQ), dietary salt, and BMI of the mother.

At the age of 5-6 years

Body height and weight, smoking exposure, FFQ, dietary salt, and physical activity.

Between birth and the age of 6 years

Periodic measurements of height and weight, collected by the CHC.Periodic measurements of gross motor skills, collected by the CHC.

For the prediction models to estimate the risk of poor cardiometabolic outcome, with the aim to assess the need for further diagnostics (blood pressure measurements and blood tests), the aforementioned candidate predictors will be used at the age of 5-6 years. At 10 years of age, the growth measurements and any other variables that can vary over time such as passive smoking between 6 and 10 years of age will be included as well.

### Development of the Prediction Models

Dynamic risk prediction models will be developed in both cohorts. Missing values will be taken into account using advanced imputation techniques [36].

To design the dynamic risk prediction models, we will choose a statistical technique that can account for clustering of the data due to the collection of repeated measurements over time within children. This approach makes it possible to introduce repeatedly assessed risk factor information for children between birth and the age of 6 years into the model. For comparison purposes, the initial model (created at birth) will be updated with new information obtained at each visit, including the age of the child [37].

The statistical technique used in this study will be determined based on a comparison between existing simple and advanced statistical methods in order to handle repeatedly measured independent variables and a non-time-varying outcome variable in a prediction model, as described by Chen et al [38] and Tu et al [39]. We will compare the applicability of these methods for the development of prediction models for use by epidemiologists and clinical practitioners, and we will test the predictive quality of these models.

Backward selection will determine the final risk prediction models. The initial regression model, including all potential predictors, will be fitted in the dataset. To ensure sufficient power during the modeling process, we will optimize the balance between the number of variables and outcome “events” in the models [40].

Next, variables that have weak associations will be omitted from the model. We will use the Akaike information criterion (AIC) as a stopping rule to determine which variables should be removed from the model. For a single predictor, AIC equates to selection at *P*=.157 [40]. This relatively high *P* value results in the inclusion of weaker predictors in the model at the cost of potentially selecting a nuisance variable. Such a model usually performs well in new subjects [40].

### Performance of the Prediction Models

The performance of the prediction models will be studied in terms of both discrimination and calibration. Discriminative ability expresses how well the model can distinguish between preadolescent children with the outcome and preadolescent children without the outcome. Discriminative ability will be assessed with the area under the receiver operating characteristic curve [41]. To reflect how well the predicted and observed values agree, the calibration slope will be estimated in a regression model using the linear predictor as the sole variable. The linear predictor is calculated by multiplying the model’s regression coefficients with the predictor values for each child and then summing these values (including the intercept). Under ideal conditions, this slope is 1, which means that the predicted and observed probabilities agree over the entire range of predictions [42]. Furthermore, the explained variability will be assessed, providing an overall measure of performance [43]. We will also decide on the cutoff values to be used in practice, taking into account sensitivity, specificity, and positive and negative predictive values for different categories of predicted probabilities.

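### The aim is to predict new overweight, but performance and cutoffs for the overweight outcomes are not shown separately for children not yet overweight at the prediction age

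*Protocol article*

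**What the plan says.** **Aim.** The Abstract (Objective) describes tools for "dynamically predicting the development of overweight, hypertension or prehypertension" and for lipid outcomes. The Introduction speaks of "targeting primary prevention to children with the highest risk of becoming overweight" and gives the reason for acting early: "Once an individual becomes overweight, this condition is usually difficult to reverse, even among children".

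**Outcome.** Under Overweight and Poor Cardiometabolic Outcome: "The outcomes of the dynamic prediction models measured at age 10-15 years are as follows". The first item is "overweight, defined using the International Obesity TaskForce (IOTF) cutoff values", followed by abdominal overweight. Both are a status at the outcome age. Neither is conditioned on status at the time of prediction.

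**Predictors.** Candidate Predictors lists repeated heights and weights from birth to age 6. Development of the Prediction Models says that the birth model is updated at each visit.

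**Performance and cutoffs.** Performance of the Prediction Models states: "Discriminative ability expresses how well the model can distinguish between preadolescent children with the outcome and preadolescent children without the outcome". That section and Development and Pilot Testing of the Prediction Tools say that cutoffs will weigh sensitivity, specificity and predictive values, with a Delphi study of experts. Neither mentions weight status at the prediction age.

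**Children already affected.** The Introduction motivates the secondary models with "Because we cannot exclude the possibility that children may already have an adverse cardiometabolic profile at this young age". Their outcomes at 5-6 and 10 years are blood pressure and lipids, not overweight.

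**The concern.** The target of prediction is a child who will become overweight. The quantity evaluated is whether a child is overweight at 10-15 years. The two agree at birth but drift apart as children grow. By the last visits some children are already overweight, their current height and weight are in the model, and those who remain overweight count as correctly predicted. Such a prediction says little about onset, and it concerns a child whose weight status the Child Health Care centre can already measure.

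Two later decisions depend on these figures. The Delphi panel will set action cutoffs from them. The Discussion also makes high sensitivity, specificity and predictive values the condition for a randomised trial of the tools combined with primary preventive programmes. If the figures look good partly because established overweight persists, both decisions rest on a population other than the one that primary prevention of overweight addresses.

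**Working it through.** **No figure to reproduce.** The article states no AUC, event count, overweight prevalence, or BMI correlation between age 6 and the outcome age. Its only tracking figure, a correlation above 0.7 for BMI SDS in the Discussion, runs from age 10 to young adulthood. Everything below is therefore an illustration on assumed inputs.

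**Assumptions.** BMI SDS at the prediction age (X) and outcome age (Y) are bivariate normal with correlation r = 0.3, 0.5, 0.6, 0.7 or 0.8. The pairs of overweight prevalence at prediction and outcome (p_b, p_o) are 5%/15%, 10%/15%, 15%/15% and 15%/20%. The score is X alone. The cutoff flags the top 20% of all children. The article sets no such cutoff.

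**Formulas.** Let J = P(already overweight and overweight later) and K = P(flagged and overweight later).
- Share of later cases already overweight = J / p_o
- Sensitivity: all = K / p_o; not yet overweight = (K − J) / (p_o − J)
- PPV: all = K / 0.20; not yet overweight = (K − J) / (0.20 − p_b)
- Share of flagged children already overweight = p_b / 0.20

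**Worked case: r = 0.6, p_b = 10%, p_o = 15%.** The bivariate normal gives J = 0.0506 and K = 0.0811.
- Share of cases already overweight: 0.0506 / 0.15 = 0.34
- Sensitivity, all: 0.0811 / 0.15 = 0.54
- Sensitivity, not yet overweight: 0.0305 / 0.0994 = 0.31
- PPV, all: 0.0811 / 0.20 = 0.41
- PPV, not yet overweight: 0.0305 / 0.10 = 0.305
- Flagged children already overweight: 0.10 / 0.20 = 50%

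**Varying baseline overweight (r = 0.6, p_o = 15%):**

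| | All children | Not yet overweight, p_b = 5% | p_b = 10% | p_b = 15% |
|---|---|---|---|---|
| AUC | 0.81 | 0.78 | 0.77 | 0.76 |
| Sensitivity, top-20% cutoff | 0.54 | 0.43 | 0.31 | 0.17 |
| PPV, top-20% cutoff | 0.41 | 0.34 | 0.305 | 0.28 |
| Later cases already overweight | – | 20% | 34% | 45% |
| Flagged children already overweight | – | 25% | 50% | 75% |

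**Varying r as well (all 20 scenarios).** Between 11% and 61% of later cases are already overweight at the prediction age. AUC in all children exceeds AUC in the not-yet-overweight by 0.016-0.056. Sensitivity is 0.33-0.71 in all children and 0.09-0.61 in the not-yet-overweight. The direction is the same every time.

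**The case against.** **The performance sentence is a generic definition.** It does not say who is in the denominator at each visit, and a condensed article may leave risk sets to a fuller plan. This is fair as far as it goes. But the gap between predicting onset and evaluating later status is visible in the article's own aim and outcome definition, so the point does not rest on silence alone.

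**The secondary models are no evidence of an oversight.** A reader might infer that overweight was forgotten when models for already affected children were planned. The article does not support that. Those models decide who needs blood pressure and blood tests for conditions that usually cause no symptoms. Existing overweight is seen from routine height and weight and needs no detection model.

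**Overweight children remain legitimate users of the tool.** They can still be targets for preventing hypertension or abnormal lipids, and the tools also guide advice, follow-up and further diagnostics. The Discussion expects the risk estimate to predict better than current IOTF status, and testing that needs overweight children in the data. This stands. It argues against removing them from the fitted model or discarding the all-children results.

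**The illustration is not the planned model.** The real models add parental BMI, education, smoking, diet and more, so the gaps will differ. Part of the AUC difference is simply the narrower BMI range. At a fixed threshold, lower sensitivity also comes with higher specificity. In the worked case specificity rises from 1 − (0.20 − 0.0811)/0.85 = 0.86 to 1 − (0.10 − 0.0305)/(0.90 − 0.0994) = 0.91. The all-children figures are therefore not wrong. They answer a different question, which is why both sets are needed.

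**Conclusion.** The concern holds in a limited form. For overweight and abdominal overweight, at visits where overweight can already be present, the described evaluation does not show how well the tool works in children not yet overweight, who are the group named in the primary prevention aim. On the assumed inputs the effect on AUC is modest (about 0.02-0.06). The loss in cutoff sensitivity can be large once baseline overweight reaches about 10%.

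A reader might go further and infer that performance will be driven by children already overweight, or that a cutoff will mostly flag them. The documents do not support either claim. Both depend on prevalences and a tracking correlation that the article does not give. With a top-20% cutoff and a BMI-only score, already overweight children exceed half of those flagged only if baseline overweight exceeds 10%. In most scenarios most later cases are not yet overweight.

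The birth model is unaffected, infancy is little affected, and the blood pressure and lipid outcomes are outside the point. This is a cheap improvement, not a flaw that invalidates the models.

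**What to change.** Keep fitting the models in all children. At each visit where the IOTF definition can be applied, also report AUC, calibration, sensitivity, specificity, PPV and NPV for the overweight outcomes among children not overweight at that visit, beside the all-children results. State at each visit how many later cases were already overweight. Give both sets to the Delphi panel when cutoffs for preventive referral are discussed, and use the not-yet-overweight figures for any claim about primary prevention of overweight.

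The cost is one extra table from data already held, with fewer events and so wider confidence intervals at the oldest visits.

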### Validation and Updating

We will use bootstrapping techniques to internally explore the need to correct for optimism in regression coefficients and performance measures of the dynamic risk prediction models. The dynamic risk prediction models, which will be developed in the oldest cohort (PIAMA), will be externally validated in the youngest cohort (Generation R). Validation is essential in order to determine the ability of a model to reliably predict the outcome in other populations and settings. If necessary, the models will be updated based on the validation results in both cohorts. Thus, we will study whether the models either remain stable or improve by removing or adding predictors that are available in the validation data. Finally, the model will be fit to the combined PIAMA and Generation R data, with the goal of achieving optimal precision of the estimated coefficients.

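### A calibration slope of 1 does not show that predicted and observed risks agree: the stated check can pass at external validation while absolute risks are systematically too high or too low.

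*Protocol article*

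**What the plan says.** Under Performance of the Prediction Models, the article splits performance into discrimination, measured by the AUC, and calibration. The aim of the calibration part is given as "To reflect how well the predicted and observed values agree", and the measure is one quantity: "the calibration slope will be estimated in a regression model using the linear predictor as the sole variable". The linear predictor is built from the model's coefficients and the child's predictor values by "summing these values (including the intercept". That intercept belongs to the developed model. It is not one estimated in the validation data. The section then interprets the result: "Under ideal conditions, this slope is 1, which means that the predicted and observed probabilities agree over the entire range of predictions".

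Two further items stand in the same section. One is an overall measure: "the explained variability will be assessed, providing an overall measure of performance", with no index named. The other concerns use in practice: "We will also decide on the cutoff values to be used in practice", with sensitivity, specificity and predictive values considered for categories of predicted probability.

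Under Validation and Updating, the models are "developed in the oldest cohort (PIAMA), will be externally validated in the youngest cohort (Generation R". Updating is allowed if validation shows a need, and is explained as follows: "we will study whether the models either remain stable or improve by removing or adding predictors that are available in the validation data". Last, the model is refitted to both cohorts together.

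**The concern.** The sentence reverses an implication. If predicted and observed probabilities agree everywhere, the slope is 1. The article asserts the converse, that a slope of 1 means agreement. The slope describes whether predictions are spread correctly. It does not describe whether their level is right.

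The level matters here for two reasons. First, the model moves between cohorts that, by the Design and Setting section, differ in ways that could change baseline risk. PIAMA children were born in 1996-1997, are mainly Caucasian, and come from urban and rural areas. Generation R is multiethnic, from Rotterdam, and dates from 2002-2006. Second, the tools act on absolute risk. Development and Pilot Testing of the Prediction Tools ties cutoffs to advice, extra follow-up and referral, and the risks are to be communicated to parents. A model can rank children well and still give every one of them a risk that is too low or too high. The rule as written would count such a model as calibrated.

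**Working it through.** **The plan's own figure.** The article states that the slope is 1 under ideal conditions. This reproduces. With no shift between predicted and true log odds, the simulated slope is 0.999-1.005 (n = 1,000,000 per run).

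**The algebra.** The recalibration model is logit P(Y=1) = a + b × LP, where LP is the linear predictor and b the calibration slope. Suppose the true risk in the validation cohort satisfies logit P = LP + c for a constant c. Then b = 1 and a = c, whatever c is. Agreement needs a = 0 and b = 1 together, and only b is to be reported.

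**A numerical check.** Inputs: mean predicted risks of 3.5%, 9% and 19%, borrowed from the hypertension prevalences in the Introduction. Assumptions: LP normal with SD 1 (AUC about 0.75), and true odds multiplied by a constant between 0.5 and 3. Results at n = 1,000,000:

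| Mean predicted risk | Odds multiplied by | Slope | Observed risk | Top decile, predicted vs observed |
|---|---|---|---|---|
| 9% | 2 | 1.003 | 15.5% | 28.7% vs 44.0% |
| 9% | 0.5 | 0.991 | 4.9% | 28.8% vs 17.0% |
| 19% | 2 | 0.996 | 29.8% | not tabulated |
| 3.5% | 3 | 0.997 | 9.2% | not tabulated |

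In the first row O/E is 15.5/9 = 1.72 with a slope of 1. Over all these runs the AUC stays within 0.741-0.757, so it gives no warning. The shift is constant on the log-odds scale. On the probability scale the gap varies with risk: in the first row the bottom decile is 1.2% predicted against 2.5% observed.

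**At a realistic size.** Generation R follow-up is 61% of 7893: 0.61 × 7893 ≈ 4815. In one simulated sample of that size, with mean predicted risk 9.2% and odds doubled, the slope is 0.991 (SE 0.047) while the observed risk is 15.7%.

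**What recovers the shift.** The intercept of a logistic model with LP as offset (calibration-in-the-large) has true value ln 2 = 0.693 when odds are doubled. The estimates are 0.689-0.694 at n = 1,000,000 and 0.682 in the sample of 4815.

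**Cohort illustration, before and after the combined refit.** The prevalences of 12% in PIAMA and 18% in Generation R are assumed, with the same LP distribution and coefficients in both.

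- PIAMA model applied to Generation R: O/E = 18/12 = 1.50, slope 1.0.
- Pooled prevalence, with 3963 and 4815 children as upper limits for available outcome data: (3963 × 0.12 + 4815 × 0.18) / 8778 = (475.6 + 866.7) / 8778 = 0.1529.
- With one common intercept, O/E is 0.18/0.1529 = 1.18 in Generation R and 0.12/0.1529 = 0.78 in PIAMA.
- With 20% instead of 18%: O/E 20/12 = 1.67 before the refit. The pooled prevalence is then (475.6 + 963.0) / 8778 = 0.1639, giving 1.22 in Generation R and 0.73 in PIAMA.
- With 10% and 12%: O/E 12/10 = 1.2 before the refit, again at slope 1.0.

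**The case against.** A reader might infer that a wrong baseline risk would go both undetected and uncorrected. The article does not support that, for three reasons.

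- The closing refit to both cohorts re-estimates the intercept using Generation R outcomes, and the tools are built after that. This stands, but the remedy is partial. No cohort term is mentioned, a common intercept averages two baselines, and no independent cohort then remains to show the residual error.
- Predictive values by category of predicted probability come close to a grouped calibration check, and a squared-error version of explained variability would react to a shift. This also stands, but the index is unspecified and neither item is planned as a check of level. Such values, if computed in the validation or combined data, describe the cutoff as it performs. They are not made wrong by the shift.
- The updating step first speaks of updating in general. Adding and removing predictors is an elaboration that does not exclude recalibration. This stands: intercept recalibration is unnamed, not ruled out.

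A reader might also infer that a shift between these cohorts is the likely outcome. The documents give no outcome prevalence by cohort, and O/E in the illustration is simply the ratio of the chosen inputs. Ethnicity, urbanization grade, parental education and parental BMI are candidate predictors and could explain part of any difference.

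For internal validation, maximum-likelihood fitting makes the apparent mean calibration correct by construction, so the slope is the informative measure there. The concern is external validation.

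Finally, a condensed article may leave calibration plots and intercepts to a fuller plan, so their absence alone would not be a finding. The sentence itself, however, states a wrong rule.

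One technical escape fails. If the regression were meant to have no intercept, a shift would move the coefficient (0.73 for doubled odds and 1.31 for halved odds at 9% mean risk). That coefficient mixes level with spread, is not the usual calibration slope, and at a value of 1 would still not guarantee agreement over the whole range.

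**Conclusion.** The point holds as an error of interpretation in the text. The only named calibration measure cannot support the conclusion drawn from it, and the stated check could pass at external validation with absolute risks systematically wrong. This follows from the algebra and does not depend on any assumed prevalence.

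The size in this study is unknown. Under the assumption of 12% versus 18% with an unchanged linear predictor, O/E is 1.5 before the combined refit, and about 1.18 (Generation R) and 0.78 (PIAMA) after it. A smaller true difference, or one explained by the predictors, would give less.

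This should be fixed before external validation. It does not undermine the design: no data collection or irreversible step is affected, the combined refit repairs part of any shift, and other planned measures might show it indirectly.

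**What to change.** 1. Under Performance of the Prediction Models, reword the sentence: agreement requires a calibration intercept of 0 and a slope of 1, with a calibration curve to check the shape.
2. At external validation, report calibration-in-the-large (the intercept with the linear predictor as offset) or O/E, and a calibration curve, beside the slope. Report the same by cohort for the combined model.
3. Under Validation and Updating, name intercept recalibration among the updating options. The order of updating steps can stay with the investigators.

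The cost is a few sentences and a few lines of code. No new data are needed.
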